## 12.2 Treatment period

- Vital signs: Heart rate, respiratory rate, temperature, and blood pressure;
- Physical examination: Facial features, integumentary system, lymph nodes, eyes, ears, nose, throat, oral, respiratory system, cardiovascular system, abdomen, urinary tract system, musculoskeletal system, nervous system, and spiritual state;
- Blood pressure (BP) monitoring: BP is measured by the subject himself/herself and recorded in the patient diary card. BP is tested at least 3 times per week for the first 2 cycles and followed up each day if the blood pressure was abnormal. In addition, BP is measured again by the investigator at each follow-up visit, coffee and tobacco intake are prohibited within 30 minutes before each BP is measured and the measurement is taken in the sitting position with the arm at heart level after at least 10 minutes of quiet sitting, and each BP measurement is taken on the same side;
- Hemanalysis: Hemoglobin, red blood cell, white blood cells, absolute neutrophil count, lymphocyte count, and platelet count;
- Blood biochemistry: TBil, ALT, AST, ALP, r-GT, total protein, Cr, uric acid (UA), blood glucose, triglyceride, cholesterol, potassium, sodium, chlorine, calcium, urea, and phosphonium;
- Coagulation tests: PT, APTT, TT, Fbg, and INR;
- Myocardial enzymes: Creatine Kinase, Myoglobin, CK-MB, Troponin T;
- ECOG PS;
- Adverse event assessment;
- Documentation of concomitant medications and treatments;
- Tumor imaging evaluation;
- Study drug administration (for visits requiring tumor imaging evaluation, the assessment must be completed prior to drug administration).

## 12.3 End-of-treatment and withdrawal study

To be completed within 3 days after confirmed treatment discontinuation, including the following:

- Vital signs: Heart rate, respiratory rate, temperature, and BP;
- Physical examination: Facial features, integumentary system, lymph nodes, eyes, ears, nose, throat, oral, respiratory system, cardiovascular system, abdomen, urinary tract system, musculoskeletal system, nervous system, and spiritual state;
- ECOG PS;
- Hemanalysis / Blood biochemistry;
- Coagulation tests: PT, APTT, TT, Fbg, and INR;
- Myocardial enzymes;
- Tumor imaging evaluation;
- Adverse event assessment;
- Documentation of concomitant medications and treatments;
- Subsequent anti-tumor therapy.

## 12.4 Safety Follow-up

The follow-up shall be conducted at 7 days (±2 days) after the last dose of study medication and includes the following:

- Adverse event assessment;
- Documentation of concomitant medications and concomitant therapies;
- Recording of subsequent anti-tumor therapies.

Collection of adverse events begins from the signing of the ICF and continues until the end of the safety follow-up period (i.e., 7 days after the last administration of the study drug or upon screening failure).If a study participant initiates new anti-tumor therapy before the end of the safety follow-up period, only AEs/SAEs suspected to be related to the study drug will be collected from the start of the new anti-tumor therapy until the end of the safety follow-up period. Any death occurring during the safety follow-up period must be reported as an SAE, regardless of whether the participant received other treatments.

After the safety follow-up period, only SAEs considered to be related to the investigational drug will be collected. For participants following the last dose of Irinotecan liposome, clinical follow-up or telephone visits will be conducted to collect information on survival status, AEs, concomitant medications, and concomitant therapies. Investigators may schedule additional visits as needed to follow up on the resolution of AEs.

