## 3.2 Secondary Endpoints

(1) Adverse drug reactions: Any noxious, unintended response to the investigational drug(s) (Irinotecan liposome + Epirubicin) at any dose, causally related to treatment (per WHO-UMC causality assessment criteria).

(2) Recurrence-Free Survival (RFS): Time from treatment initiation to histologically confirmed tumor recurrence, radiologic progression or death from any cause.

(3) Disease Control Rate (DCR): Proportion of patients achieving complete response (CR), partial response (PR) and stable disease (SD).

Note: Tumor Response Evaluation (per RECIST 1.1 criteria):

- CR: Disappearance of all target lesions; no new lesions.
- PR: ≥30% decrease in the sum of diameters of target lesions.
- SD: Neither sufficient shrinkage to qualify for PR nor sufficient increase to qualify for progressive disease (PD).
- PD: ≥20% increase in the sum of diameters of target lesions or appearance of new lesions.

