## 4.1 Overall design

Enrolled patients with anthracycline-resistant recurrent NMIBC will first undergo enhanced pelvic-abdominal MRI and cystoscopy to collect imaging and pathological data. Two senior urologists will determine whether the tumor is resectable via TURBT. If unresectable (Arm A), patients will receive neoadjuvant irinotecan liposome combined with Epirubicin per the dose-escalation protocol. Post-treatment efficacy will be assessed by contrast-enhanced pelvic-abdominal MRI. For patients with CR and PR, TURBT with intravesical therapy was performed following confirmation by two independent senior urologists. For patients with SD or PD, subsequent therapies were determined by the investigator’s discretion. If resectable (Arm B), TURBT will be performed followed by immediate intravesical Epirubicin (50 mg) instillation within 24 hours postoperatively. During the induction phase (weeks 1-4 post-TURBT), the treatment with irinotecan liposome combined with Epirubicin will be completed according to the dose - escalation regimen. During the maintenance phase (months 1-6 post-TURBT), intravesical maintenance instillation of Epirubicin will be conducted once a month for a total of 6 cycles. The safety and adverse reactions will be followed up from the induction phase, and the tumor recurrence will be assessed by pelvic and abdominal enhanced MRI and cystoscopy after combination treatment.

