# 10. Concomitant Medications

All concomitant medications must be recorded in the Case Report Form (CRF), and the concomitant medications/treatments should be recorded from 28 days before the first dose to 30 days after the last dose. If a new antineoplastic therapy was initiated within 30 days after the last dose of the study drug, only concomitant medications/treatments for adverse events related to the study drug were recorded. After 30 days of the last dose, only concomitant medications/treatments used for follow-up for adverse events were recorded.

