## 14.3 Collection/follow-up of AE/ SAEs

### 14.3.1 Collection of AE/SAE

The collection of AE/SAE information shall begin from the signing of the ICF and continue until the end of the safety follow-up period (defined as 30 days after the last administration of the investigational product) or Screening failure, whichever occurs first.

If a study participant initiates new anti-tumor therapy prior to the completion of the safety follow-up period, only AE/SAEs suspected to be related to the investigational product shall be collected from the start of the new anti-tumor therapy until the end of the safety follow-up period.

Any death occurring during the safety follow-up period must be reported as an SAE, irrespective of whether the participant received other treatments.

For all AEs occurring in study participants, investigators must maintain detailed documentation including: AE name, Start and end dates, Severity grade, Relationship to the investigational product, Duration, Actions taken regarding the investigational product, Outcome and Whether the event meets SAE criteria.

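### Sections 12.4 and 14.3.1 end the same safety follow-up period at 7 days and at 30 days after the last dose, and nothing says which governs

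*Protocol*

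**What the plan says.** Section 12.4 starts adverse-event collection at consent and ends it with the safety follow-up period, specified as "7 days after the last administration of the study drug or upon screening failure". The visit is timed to match: "The follow-up shall be conducted at 7 days (±2 days) after the last dose of study medication". For what comes later, the section states: "After the safety follow-up period, only SAEs considered to be related to the investigational drug will be collected". The next sentence says that, after the last irinotecan liposome dose, "clinical follow-up or telephone visits will be conducted to collect information on survival status, AEs, concomitant medications, and concomitant therapies". No schedule or end date is attached to those contacts.

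Section 14.3.1 also starts at consent and also ends with the safety follow-up period, but that period is "defined as 30 days after the last administration of the investigational product". It covers both AEs and SAEs.

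Section 10 records concomitant medication "from 28 days before the first dose to 30 days after the last dose".

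Section 3.2 lists adverse drug reactions as the first secondary endpoint: "Any noxious, unintended response to the investigational drug(s) (Irinotecan liposome + Epirubicin) at any dose, causally related to treatment". It sets no time window.

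On the drugs, the synopsis entry for study drug and the drug overview in Section 8 list irinotecan liposome only, whereas Section 3.2 names irinotecan liposome and epirubicin together.

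**The concern.** Two sections that give operating instructions to site staff assign different lengths to one named period, and staff cannot follow both. This decides which events are recorded at all, so it cannot be left to the analysis stage: an event never collected cannot be recovered. The adverse drug reaction endpoint has no window of its own and depends entirely on these two sections.

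Other duties hang on the same period. Every death within it is an SAE (12.4 and 14.3.1), and deaths possibly due to progression within it are SAEs (14.6). Return visits for combined transaminase and bilirubin abnormalities refer to it (14.4), and so does one of the end-points for following up an event (14.3.2). Each inherits the ambiguity.

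Safety is the main purpose of this phase I study and the arms are small, so a few events captured under one reading and missed under the other would change the reported profile visibly.

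**Working it through.** The plan gives no derived figure to reproduce. The check sets the sections side by side and subtracts the stated windows.

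**1. Length of the gap.** Inputs: 7 days (12.4) and 30 days (14.3.1).
- 30 − 7 = 23 days, that is, onset on days 8 to 30 after the last dose.
- The 12.4 visit falls on day 7 ± 2, so on days 5 to 9. From that visit to day 30 is 30 − 9 = 21 to 30 − 5 = 25 days.

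**2. What is collected for onset on days 8 to 30.**

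| Event | Under 12.4 | Under 14.3.1 |
|---|---|---|
| Related SAE | Collected | Collected |
| Non-serious adverse reaction, non-serious grade 3 included | Outside | Collected |
| Unrelated non-serious AE | Outside | Collected |
| Unrelated SAE | Outside | Collected |
| Death, any cause | Only if a related SAE | Always reported as an SAE |

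The 12.4 column applies its related-SAE rule. The sentence on later contacts in the same section points the other way. With no schedule or end date it does not settle the matter; it makes 12.4 inconsistent with itself.

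**3. Anchor drug.** The protocol gives no day numbers for dosing. Assume irinotecan liposome on days 1 and 15 and weekly epirubicin on days 1, 8, 15 and 22. Arm A collection then ends on:

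| Last dose taken as | 7-day rule | 30-day rule | Ratio |
|---|---|---|---|
| Irinotecan liposome, day 15 | 15 + 7 = day 22 | 15 + 30 = day 45 | 45/22 = 2.0 |
| Epirubicin, day 22 | 22 + 7 = day 29 | 22 + 30 = day 52 | 52/29 = 1.8 |

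In Arm A the choice of anchor moves the end by 22 − 15 = 7 days. In Arm B it moves it by roughly six months, because epirubicin maintenance runs monthly for six cycles (4.1 and 4.2). If irinotecan liposome alone is the anchor, most or all of maintenance lies outside routine AE collection.

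**4. Weight of one event.** Section 5 plans 6 to 9 participants per arm. One participant whose only event falls in the gap changes an arm's incidence by 1/9 = 11 to 1/6 = 17 percentage points. This is the size per missed participant, not a forecast of how many would be missed.

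**The case against.** The best defence is that the damage is limited. Related SAEs are captured under either section. DLTs are assessed in an evaluation period during treatment, so the primary endpoint is not directly touched. The affected endpoint is secondary, in 12 to 18 participants. Section 12.4 also foresees later clinic or telephone contacts that ask about AEs. The first three points stand and bound the finding. The last means one cannot say flatly that recording stops, but it does not resolve a conflict with the sentence immediately before it.

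Several stronger readings are tempting, and the documents do not support them:

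- **The endpoint has two definitions.** It has one, causal and without a time limit (3.2). Only the collection window conflicts.
- **The start of collection also conflicts.** Section 4.1 says "The safety and adverse reactions will be followed up from the induction phase", which might be read as leaving out the immediate instillation in Arm B. But 12.4 and 14.3.1, which govern collection, agree on consent. The synopsis describes induction as the first month after surgery, which can include that instillation. This is loose overview wording.
- **The end of collection varies 2.4-fold.** The ratio 52/22 mixes two anchors. With one anchor held fixed it is 2.0 or 1.8.
- **Some 77% of post-treatment events would be lost.** The fraction 23/30 describes calendar time. Reading it as a share of events needs uniform onset, for which the protocol gives no basis, and it would wrongly count related SAEs as lost.
- **Prolonged late-onset diarrhea would be missed.** A collection window governs new onsets. Duration is covered by the follow-up rule in 14.3.2, and Section 9.2 gives no onset time beyond the first week.

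**Conclusion.** The contradiction holds. One named period, with one start, has two end dates 23 days apart, and no text in the protocol ranks them. What is at stake is the capture, on days 8 to 30 after the last dose, of non-serious adverse reactions, of unrelated AEs and SAEs, and of deaths not judged to be related SAEs. The 23-day gap rests on the stated text alone. The calendar in step 3 rests on the assumed dosing days. The number of events affected cannot be estimated from the protocol.

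Two related faults belong with it: the post-window rule in 12.4 conflicts with the sentence that follows it, and the reference dose is ambiguous between irinotecan liposome alone and either drug. The second matters little in Arm A and a great deal in Arm B.

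**What to change.** State one collection window in Sections 12.4 and 14.3.1: from consent to a single number of days after the last dose of either study drug, with both drugs named. Then:

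- align the timing of the safety follow-up contact with the end of that window;
- reword the post-window rule in 12.4 so that it and the sentence on later contacts agree on what is collected and until when;
- bring the start wording in 4.1 into line with collection from consent.

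The sponsor must settle the length. A 30-day window captures everything that a 7-day window does and already matches the concomitant-medication window in Section 10, so it needs the fewest further changes. Events with later onset, other than related SAEs, would still fall outside it.

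The cost is wording changes in these sections and, if 30 days is kept, one later adverse-event contact per participant, for which Section 12.4 already allows the telephone.

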## 12.5 Survival Follow-up

RFS follow-up was conducted every 2 months from the last dose of medication to collect RFS information and post-study treatment information (including subsequent antineoplastic therapy and efficacy) until death or loss of follow-up or discontinuation of the study.

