| Endpoints | 1. Primary Endpoints:  Incidence and frequency of Dose-Limiting Toxicity (DLT)  2. Secondary Endpoints:  (1) Adverse drug reactions;  (2) Recurrence-Free Survival (RFS);  (3) Disease Control Rate (DCR);  3. Tumor Response Evaluation (per RECIST 1.1 criteria):   - Complete Response (CR): Disappearance of all target lesions; no new lesions. - Partial Response (PR): ≥30% decrease in the sum of diameters of target lesions. - Stable Disease (SD): Neither sufficient shrinkage to qualify for PR nor sufficient increase to qualify for PD. - Progressive Disease (PD): ≥20% increase in the sum of diameters of target lesions or appearance of new lesions. |
| Study Procedures | 1. Arm A: TURBT unresectable  If the recurrent tumor can't be excised by TURBT, participants will be assigned to this arm. Participants in this arm will complete the neoadjuvant therapy with Irinotecan liposome (intravenous injection, once every two weeks for 1 month, dose increasing regimen: 37.6 mg/m^2^ and 56.5mg/m^2^) and Epirubicin (intravesical instillation, once a week for 1 month, 50 mg), and the therapeutic effect was evaluated by pelvic enhanced MRI and cystoscopy. Judged by two senior urologists, patients with complete response and partial response were treated with TURBT and intravesical therapy. Patients with stable disease or progressive disease received subsequent therapy at the investigator's discretion. Participants will visit the clinic once every 2 weeks for checkups and tests.  2. Arm B: TURBT resectable  If the recurrent tumor can be excised by TURBT, participants will be assigned to this arm (Arm B). Participants in this arm will complete TURBT with immediate intravesical instillation of Epirubicin (50 mg) within 24 hours after surgery. During the induction phase (the first 1 month after surgery), participants will receive the combined therapy with irinotecan liposome (intravenous injection, once every two weeks for 1 month, dose increasing regimen: 37.6 mg/m^2^ and 56.5mg/m^2^) and Epirubicin (intravesical instillation, once a week for 1 month, 50 mg). In the next 6 months, participants will continue the intravesical instillation treatment with Epirubicin (once a month, 50 mg). Participants will visit the clinic once every 2 weeks for checkups and tests in the first month, and once every 3 months after the first month. |

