| Termination Criteria | The study may be prematurely terminated or temporarily suspended based on the following criteria:  1. Identification of unexpected, significant, or unacceptable risks to study participants  2. Discovery of critical protocol flaws during trial execution |
| Safety | Any adverse events (AEs) that occurred in all subjects during the clinical study period will be observed, including abnormal clinical symptoms and vital signs, and abnormalities in laboratory tests. The clinical characteristics, severity, time of occurrence, duration, treatment methods, and prognosis of adverse events will be recorded; meanwhile, the correlation between adverse events and the study drugs will be determined. The safety of drugs is evaluated according to National Cancer Institute's Common Terminology Criteria for Adverse Events (NCI-CTC AE) version 5.0. |
| Statistical Analysis | For the primary endpoint, the DLT Analysis Set (DAS) included all participants who were in the DLT evaluation period and either completed the DLT assessment or experienced a DLT during the evaluation period. This analysis set will be used for the analysis and summary of DLT events.  For Secondary Endpoints, such as RFS, the median value and 95% CI are estimated and survival curves are obtained using the Kaplan-Meier method. The log-rank test is used to compare the survival between the two groups. DCR with 95% CI are calculated, and comparisons between treatment groups are performed using a Cochran-Mantel-Haenszel (CMH) test or chi-square test. Two independent samples will be compared for the differences between the two groups in QoL scores by the t-test or Wilcoxon rank sum test. |
| Study Schedule | Enrollment date of the first subject: January 2025  Estimated date of the primary completion date: April 2025  Estimated date of the end of the study: December 2025 |

1. Background

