## 1.1 Overview of Bladder Cancer

Bladder cancer has emerged as one of the most common genitourinary malignancies in China, currently ranking as the eighth most frequently diagnosed cancer among Chinese male populations. With its characteristically high incidence, frequent recurrence patterns, and substantial mortality burden, this disease represents a major public health challenge in contemporary China [1]. Among histological subtypes, non-muscle invasive bladder cancer (NMIBC) constitutes approximately 75% of incident cases at initial diagnosis, representing the predominant clinical presentation. This form demonstrates particularly aggressive recurrence patterns, with published 5-year recurrence rates ranging from 31% to 78% across various clinical series [2]. The substantial recurrence risk, coupled with potential progression to muscle-invasive disease, underscores the critical need for effective therapeutic interventions. To mitigate recurrence and disease progression, adjuvant intravesical instillation therapy following transurethral resection of bladder tumor (TURBT) has been established as the standard treatment regimen for NMIBC.

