### 15.5.3 Statistical Method

For the primary endpoint, the DLT Analysis Set (DAS) included all participants who were in the DLT evaluation period and either completed the DLT assessment or experienced a DLT during the evaluation period. This analysis set will be used for the analysis and summary of DLT events. DLT Rate = ( Number of participants with ≥1 DLT / Total evaluable participants in DAS)×100%. 95% CI will be computed using the Clopper-Pearson method.

For Secondary Endpoints, such as RFS, the median value and 95% CI are estimated and survival curves are obtained using the Kaplan-Meier method. The log-rank test is used to compare the survival between the two groups. DCR with 95% CI are calculated, and comparisons between treatment groups are performed using a Cochran-Mantel-Haenszel (CMH) test or chi-square test. Two independent samples will be compared for the differences between the two groups in QoL scores by the t-test or Wilcoxon rank sum test.

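### RFS visits are timed from an undefined last dose, so event dating may differ by arm; separately, the planned 95% CI for median RFS is very unlikely to have an upper limit

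*Protocol*

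**What the plan says.** Section 3.2 defines RFS as "Time from treatment initiation to histologically confirmed tumor recurrence, radiologic progression or death from any cause". Section 12.5 then says "RFS follow-up was conducted every 2 months from the last dose of medication to collect RFS information". It does not say which drug's last dose is meant.

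Treatment length differs between the arms. Arm A has about one month of combination treatment. Arm B has the same month and then monthly epirubicin. Section 4.1 places this maintenance in months 1-6 after TURBT and says "intravesical maintenance instillation of Epirubicin will be conducted once a month for a total of 6 cycles". The synopsis places it in the six months after the first month.

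For clinic visits, the synopsis sees Arm B every two weeks in the first month and "once every 3 months after the first month", with no stated end. Sections 4.1 and 4.4 put MRI and cystoscopy after the combination treatment.

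For the analysis, section 15.5.3 says that "the median value and 95% CI are estimated and survival curves are obtained using the Kaplan-Meier method", and it adds a log-rank test between the two groups. Section 5 plans 6-9 participants per arm. The synopsis has the first enrolment in January 2025, primary completion in April 2025, and "Estimated date of the end of the study: December 2025".

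**The concern.** There are two separate issues.

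The first is how events are dated. A recurrence found by cystoscopy or imaging is dated when someone looks. If looking is timed from the end of treatment and treatment lasts one month in one arm and six or seven in the other, the arms are assessed on different clocks. Late detection lengthens apparent RFS in the arm that is examined later. That difference would then enter the planned log-rank comparison.

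The second is the choice of summary. The median with its 95% CI is the only numerical RFS estimate that the protocol names. If arm size and follow-up cannot support the interval, the report will have a curve and an incomplete interval, with no RFS figure fixed in the protocol to fall back on.

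**Working it through.** The protocol gives no expected median, event count or power for RFS, so there is no figure of its own to reproduce.

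**Step 1: visit calendar (months from treatment start).** The first 12.5 visit is the last dose plus 2 months.

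| Last dose taken as | Arm A | Arm B |
|---|---|---|
| Last epirubicin | 1 + 2 = 3 | 6 + 2 = 8 (section 4.1) or 7 + 2 = 9 (synopsis) |
| Last irinotecan liposome (about month 0.5-1.5) | 2.5-3.5 | 2.5-3.5 |

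The Arm A epirubicin entry counts only the neoadjuvant month.

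Assume that entry runs from January to March 2025, because DLT observation has to fit before primary completion in April. Follow-up to the end of December 2025 is then about 9-12 months. On the epirubicin reading, an Arm B participant has between one visit (late entrant) and three visits (January entrant, last dose at month 6) under 12.5.

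**Step 2: dated recurrence assessments in Arm B before month 8-9 (epirubicin reading).**
- MRI and cystoscopy after combination treatment: about month 1.
- Clinic visits at 1 + 3 = 4 and 4 + 3 = 7 months: neither cystoscopy nor MRI is specified.
- End-of-treatment assessment (section 12.3): lists tumour imaging but not cystoscopy. It is tied to treatment discontinuation, so for a participant who completes maintenance it comes no earlier than month 6-7.

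The text at hand therefore dates no cystoscopy in Arm B between about month 1 and month 8-9.

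**Step 3: the two intervals.** Up to the last dose, 3-monthly visits followed by 2-monthly ones can be read as a sequence. After it they cannot both hold: the 3-monthly series continues to month 10, while 12.5 gives months 8 and 10 or months 9 and 11.

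**Step 4: can the median be reached?** Section 1.1 cites "published 5-year recurrence rates ranging from 31% to 78" per cent, for NMIBC in general. Assuming exponential times, the monthly rate is −ln(1 − p)/60 and the median is ln 2/rate.
- p = 0.31: rate 0.00618, median 112 months; 5.4% recurred by month 9 and 7.2% by month 12.
- p = 0.78: rate 0.02524, median 27.5 months; 20.3% by month 9 and 26.1% by month 12.

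The chance that at least half an arm has an event by month 12, at the higher rate, is P(≥3 of 6) = 19% and P(≥5 of 9) = 6%.

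The trial population may recur faster, so the true median was varied by simulation: 1,500 runs, entry uniform over 3 months, end at month 12, events detected only at visits, log-log limits. With visits at months 1, 9 and 11:

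| True median (assumed) | Median reached, n=6 / n=9 | Upper 95% limit reached, n=6 / n=9 |
|---|---|---|
| 6 months | 91% / 87% | 16% / 23% |
| 9 months | 74% / 61% | 8% / 10% |
| 12 months | 53% / 39% | 4% / 5% |
| 18 months | 31% / 16% | 3% / 2% |
| 27.5 months | 14% / 6% | 2% / 1% |

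**Step 5: does the visit schedule drive this?** At a true median of 12 months, the median is reached in 53% / 39% of runs with visits at months 1, 9 and 11. The figures are 51% / 39% with the 3-monthly visits added, and 53% / 40% with 2-monthly visits from the last irinotecan dose. It does not.

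**Step 6: why the upper limit fails.** With no censoring, the upper limit of the median exists only once the upper limit of S(t) is at or below 0.5. Take n = 6 after five events, so S = 1/6. The Greenwood sum is (1 − S)/(nS) = 0.833, and the log-log standard error is √0.833/1.792 = 0.509. The upper limit is exp(−exp(0.583 − 1.96 × 0.509)) = 0.517, still above 0.5. With n = 9 after seven events the same formula gives 0.513. Untransformed limits are only slightly kinder: they need five events of six (0.465) or seven of nine (0.494).

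**The case against.** The best defence is that 12.5 follows the end-of-treatment and safety sections and describes the post-treatment phase only. The synopsis names irinotecan liposome as the study drug, and section 12.4 ties part of its follow-up to that drug's last dose. On that reading the arms are seen at nearly the same time. This is a fair reading, but section 3.2 counts both drugs as investigational, so the text does not settle it. Arm A's anchor is open too, because responders go on to TURBT and intravesical therapy.

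A reader might infer that Arm B goes unobserved until month 8-9. The documents do not support that. MRI and cystoscopy follow the combination treatment, tumour imaging is listed for the treatment period (section 12.2, without dates) and at end of treatment, and unscheduled examinations are allowed. The flowchart cited in section 12 is not in the text at hand and may fix dates, though it would not reconcile the wording of 12.5 with the synopsis.

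A reader might also infer that the sparse visits are what put the median out of reach. Step 5 shows otherwise: short follow-up and small arms do that.

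Finally, curves and a log-rank test are planned besides the median, and a landmark rate can be read from a curve. That is true, but the numerical estimate that the protocol fixes is still the median with its interval.

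**Conclusion.** The point holds in a limited form.

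**Visit timing.** The anchor is undefined and does not match the RFS origin. On the epirubicin reading, the first 12.5 visit comes about 5-6 months later in Arm B than in Arm A (8 − 3 or 9 − 3). Later dating of Arm B recurrences is then possible but not certain. On the irinotecan reading the gap disappears. The 2-monthly and 3-monthly intervals conflict only after the last dose.

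**Median RFS.** The upper 95% limit is very unlikely to be reached: at most 23% of runs in every scenario and visit schedule tried, including a true median of 6 months. It would be too strong to say that the median itself cannot be estimated. It is unlikely to be reached at the protocol's general NMIBC rates, roughly an even chance at a true median of 12 months, and more likely than not at 9 months or less.

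These results assume exponential times, entry from January to March 2025, no dropout, and log-log limits. RFS is a secondary endpoint of a phase I DLT study, so this is an improvement that should be made. It does not threaten the primary objective.

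**What to change.** 1. In 12.5, state which dose starts the post-treatment follow-up. Reconcile 12.5, 4.1 and the synopsis on the end of maintenance and on the visit interval after the last dose.
2. Time RFS assessments from treatment start (TURBT in Arm B) on one schedule common to both arms, and state which visits include cystoscopy and MRI. Use existing visits where possible; Arm B already attends monthly for instillation.
3. In 15.5.3, make the Kaplan-Meier RFS probability at a fixed time, such as 6 months, with 95% CI the numerical estimate, and give the median only if reached. Under the assumed entry period every participant has at least 9 months of potential follow-up, so a 6-month estimate is within reach. Its interval will still be wide with 6-9 per arm.

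Item 3 depends on item 2: if Arm B has no recurrence cystoscopy between about month 1 and month 8-9, recurrences in that gap could be dated after month 6 and the 6-month rate would look too good.

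The cost is mostly wording. Some cystoscopy or MRI assessments may have to be re-timed or added, and the reported summary becomes a landmark rate instead of a median.
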